For this trial, a maximum of 500 patients for whom a percutaneous procedure in the thoraco-abdominal area under CT guidance has been prescribed will be enrolled in the study across the nine participating hospitals. The trial is structured as a standard two-arm, parallel-design, individually randomised trial*.* Patients are randomly assigned to the experimental arm of the trial in which procedures are carried out using navigation assistance (the NAV group), where the procedures are carried out using navigation assistance supplied by the medical device under evaluation (IMACTIS-CT®), or to the active comparator arm of the trial in which procedures are carried out guided by conventional CT (CT group), where the procedures are carried out under conventional CT guidance. The randomisation is stratified by centre and by the expected difficulty of the procedure. The assignment is open label for both the radiologist and patient.

Because a previous clinical trial has already demonstrated improved needle placement accuracy in navigation-assisted procedures using the IMACTIS-CT® device (4.1 mm [2.7–9.1]) compared with conventional procedures (8.9 mm [4.9–15.1], *p* < 0.001) according to ITT analysis [29], the aim of this trial is therefore to evaluate the clinical benefit of the navigation system. The primary outcome is a combined criterion composed of three different criteria which assess, respectively, the safety, efficacy and performance of navigation-assisted CT-guided procedures by comparing the results obtained in the navigation-assisted group with those obtained in the conventional group. The criteria will be evaluated by a blinded expert committee. It will be determined that the navigation system represents a clinical benefit if non-inferiority in terms of safety, efficacy and superiority in terms of performance is obtained in the navigation-assisted group with respect to the conventional group. Also evaluated, in terms of secondary outcomes, are (1) the duration of the procedure, (2) the satisfaction of the operator and (3) the irradiation dose delivered, with (4) subgroup analysis according to the expected difficulty of the procedure, as well as an evaluation of (5) the usability of the device.

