An initial CT scan of the patient is acquired before assignment of the patient into the experimental or comparator arm of the trial. First, landmarks are made on the patient’s skin using metal wire or a metal grill (required for conventional CT guidance), and the electromagnetic transmitter of the navigation system is attached to the patient’s skin (required for navigation-assisted CT guidance). The CT scan is then acquired, and it is verified that the procedure originally prescribed is maintained and that the navigation system is available and working. If the originally prescribed procedure is no longer maintained or the navigation system is not available or not working, the patient is removed from the study, and the procedure is carried out under conventional CT guidance.

Otherwise, the radiologist estimates the expected difficulty of the procedure on the basis of the initial CT scan. A procedure is expected to be difficult if the needle path is on a plane that is oblique to the acquired axial images, the target moves with respiration, the procedure is a lung biopsy, the target is difficult to reach (due to small size or depth of location) or the needle path is very narrow. Difficult interventions are associated with an increased risk of major complications and of procedure failure and also with an increase in the number of control scans required compared with standard interventions. Because these risks have a direct impact on the three criteria that constitute the primary outcome of the study, respectively, safety, efficacy and performance, the random assignment of the patient into the experimental or comparator arm of the trial is stratified by the expected difficulty of the procedure as well as by centre.

The expected difficulty of the procedure is entered into the electronic case report forms (eCRFs) provided by Medsharing (Fontenay Sous Bois, France; www.medsharing.fr), and the patient is then randomly assigned to the experimental (NAV) or comparator (CT) arm of the trial. The randomisation lists are generated by Medsharing using a randomisation by minimisation algorithm. By acquiring the CT scan before randomisation, it can be verified that the originally prescribed procedure is maintained and that the navigation system is available and working before the patient is assigned to the CT or NAV group, thereby minimising the later imputation of missing data for the statistical analysis.

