### Statistical analysis

The number of patients to be enrolled in the study is calculated as the maximum of the values calculated for each of the three different criteria (safety, efficacy and performance) that constitute the primary outcome, with the alpha level set to 5%. The calculations are performed as follows for each of the three criteria:
*Safety*: The suggested threshold for all major complications resulting from percutaneous drainage or biopsy procedures is 10% [31, 32]. The threshold is increased to 20% for lung procedures [33]. Because one of the participating hospitals is a referral centre for lung procedures, it has been decided to define the threshold for all major complications as 12% for this study (calculated as the average threshold across the centres, 12 = (10 × 8 + 20 × 1)/9, rounded up to the nearest whole number). Considering an initial complication rate of 5% in each of the groups, a sample size of 384 patients (192 in each of the experimental and comparator arms of the trial) will be sufficient to demonstrate non-inferiority between the groups, respecting a non-inferiority cut-off δ = 7%, with 90% power and a 5% significance level.
*Efficacy*: The minimum threshold for intervention success is 80%. Considering an initial success rate of 91% in each of the groups, a sample size of 380 patients (190 per group) will be sufficient to demonstrate non-inferiority between the groups in terms of success, respecting a non-inferiority cut-off δ = −10%, with 90% power and a 5% significance level.
*Performance*: Considering that use of the navigation system will decrease the number of control scans acquired by 20% compared with conventional procedures (estimated from previous clinical trial), a sample size of 222 patients (111 per group) will be sufficient to demonstrate superiority in the NAV group compared with the CT group in terms of a decrease in the number of control scans acquired, with 90% power and a 5% significance level.

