Estimating the loss to follow-up and the withdrawal of consent to be 4%, a minimum of 200 participants will be enrolled per group. Because the study was initially designed with the participation of eight hospitals, and to minimise a centre bias, the number of patients to be included per hospital was set at 50 ± 15. After inclusion had begun, a ninth centre requested to participate in the study. Because inclusion had already begun, the number of inclusions per centre was maintained, and the maximum sample size was defined to be 500. The study protocol was therefore modified, and the modifications were approved by the French Health Authority (Agence Nationale de Sécurité des Médicaments et des Produits de Santé) and the relevant ethics committee (Comité de Protection des Personnes, Sud-Est V, France). The sample size calculations were carried out using nQuery Advisor® 7.0 software (Statistical Solutions, Cork, Ireland) with the method ‘upper confidence limit for difference in proportions (simulation)’ [34] for the safety and efficacy criteria and Noether’s method ‘sample size determination for some common nonparametric statistics’ [35] for the performance criterion.

For the statistical analysis of the data, because non-inferiority tests are used to evaluate the safety and efficacy criteria, a PP analysis will be carried out on the data, comparing the 90% two-sided confidence interval of the difference between the proportions with the non-inferiority cut-off. Conversely, because a superiority test is used to evaluate the performance criterion, an ITT analysis will be carried out on this data, comparing the means of the two groups using Student’s *t* test or the non-parametric Mann-Whitney *U* test. For all calculations, a threshold of *p* < 0.05 is considered significant.

For the secondary outcome analysis, the means of the two groups will be compared using Student’s *t* test or the non-parametric Mann-Whitney *U* test for each outcome. Furthermore, subgroup analyses according to the difficulty of the procedure will be carried out. ITT and PP analyses will be carried out for the secondary outcomes to ensure the robustness of the results [36].

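### Allocation is minimised on centre and expected difficulty, but the named performance test ignores both and the safety and efficacy intervals read as unstratified, so the tests are conservative

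*Protocol article*

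**What the plan says.** Study design and setting states: "The randomisation is stratified by centre and by the expected difficulty of the procedure". Methods repeats that the assignment "is stratified by the expected difficulty of the procedure as well as by centre" and gives the mechanism: "The randomisation lists are generated by Medsharing using a randomisation by minimisation algorithm". The reason offered is that difficult procedures carry more major complications, more failures and more control scans: "Because these risks have a direct impact on the three criteria that constitute the primary outcome of the study".

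Statistical analysis then fixes the primary comparisons. For performance, "an ITT analysis will be carried out on this data, comparing the means of the two groups using" Student's t test or the Mann-Whitney U test. For safety and efficacy, a per-protocol analysis is planned, "comparing the 90% two-sided confidence interval of the difference between the proportions with the non-inferiority cut-off". No stratum or covariate is named for any of the three. In that section the two factors return only in the subgroup analysis (difficulty) and in the rule for filling missing values (centre and difficulty).

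**The concern.** Minimisation on a prognostic factor makes the arms more alike than simple randomisation would, so the treatment difference varies less from trial to trial. A two-sample standard error does not know this. It keeps the variation between centres and between difficulty levels as if it were noise in the comparison. The p-value is then too large and the interval too wide, and a test run at 5% rejects less often than 5% under the null.

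At stake is whether the tests deliver the level they state, and how tight the intervals are that will be compared with the margins. The error is on the cautious side: it makes neither a superiority claim nor a non-inferiority claim easier to reach.

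**Working it through.** **Inputs from the protocol article.** Nine centres and two difficulty levels; minimisation; 5% level. Safety: 5% complications in each arm, margin 7%, 90% power, 192 per arm. Efficacy: 91% success in each arm, margin 10%, 190 per arm. Performance: 20% fewer scans, 90% power, 222 patients in all. Enrolment: at least 200 per arm, at most 500 in total.

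**Assumption.** The share of outcome variance explained by centre and difficulty, R², is not given. The range examined is 10-30% for scan counts.

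**1. The plan's own sample size is an unstratified calculation.** Safety, one-sided 5%:

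n = 2 × 0.05 × 0.95 × (1.645 + 1.282)² / 0.07² = 167 per arm; with a continuity correction, 194.

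The stated 192 agrees within about 1%, and exact power at 192 per arm with the corrected limit is 89.9%. Dropout: 192 / 0.96 = 200 per arm, as stated. No strata enter. For performance, Noether's formula N = (1.960 + 1.282)² / [3(p − 0.5)²] with N = 222 implies p = 0.626, again a plain two-group figure.

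**2. Size of the distortion.** With good balance, the unadjusted standard error is too large by the factor 1/√(1 − R²), and the true two-sided level is about 2Φ(−1.96/√(1 − R²)). For R² of 10%, 20% and 30% this formula gives levels of about 0.039, 0.028 and 0.019.

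**3. Simulation.** Minimisation on nine centres and two difficulty levels (80% chance of the favoured arm, an assumption), with R² split equally between the two factors. The outcome was normal, with an effect of 0.435 SD, which gives 90% power at 111 per arm. The t test was compared with a linear model holding both factors as main effects (2,500 null and 1,500 power replicates).

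| R² | SE ratio | Type I error of t test, N = 222 / 384 | Power at N = 222, unadjusted / adjusted | Power at N = 384, unadjusted / adjusted |
|---|---|---|---|---|
| 0 | 1.00 | 0.059 / 0.050 | 89.6% / 89.5% | 98.3% / 98.3% |
| 10% | 1.05 | 0.041 / 0.046 | 89.5% / 91.7% | 99.3% / 99.3% |
| 20% | 1.12 | 0.039 / 0.029 | 91.3% / 94.0% | 99.5% / 99.9% |
| 30% | 1.19-1.20 | 0.024 / 0.015 | 93.9% / 97.0% | 99.5% / 99.9% |

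The Monte Carlo standard error of a 5% rate is √(0.05 × 0.95 / 2500) = 0.004. The adjusted model's null rates ran from 0.048 to 0.060. That test is exact for these simulated data, so the spread is noise.

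At the enrolment floor of 400, Noether scaling of the unadjusted test gives 3.242 × √(400/222) − 1.960 = 2.39, which is about 99% power.

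**4. Binary criteria.** With half the cases difficult (assumed), R² = (half the gap between the two rates)² / [p(1 − p)].

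- Safety, 2% vs 8%: 0.03² / 0.0475 = 1.9%, interval 1.0% too wide. With 1% vs 9%: R² 3.4%, interval 1.7% too wide.
- Efficacy, 97% vs 85%: 0.06² / 0.0819 = 4.4%, interval 2.3% too wide. With 99% vs 83%: R² 7.8%, interval 4.2% too wide.

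Asymptotic power goes from 93.4% to about 94% for safety and from 96.1% to about 97% for efficacy.

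**The case against.** The strongest reply is that nothing planned is lost. The sample sizes were computed without strata and the analysis follows suit, so adjustment only adds to power that is already sufficient. The error is conservative, so no false claim becomes easier. The size rests on an R² the article does not give, and at R² = 0 it vanishes. All of this stands, and it limits the point to one of efficiency and calibration.

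It also stands that only the performance test is explicitly unadjusted. For the two proportions no interval method is named, so unstratified is the natural reading rather than a statement, and the method could be set in an analysis plan not shown here.

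The remedy is not quite free. Centre by difficulty makes 18 cells, or 22 to 28 patients each at 400 to 500. Minimisation on the margins need not balance the arms within a cell. At a 5% complication rate, 400 patients yield about 20 major events, roughly one per cell.

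What the reply does not remove is the mismatch itself. The article calls difficulty prognostic for every primary criterion, balances on it, and then names a scan-count test that cannot use it.

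**Conclusion.** The point holds as a worthwhile improvement, not as a threat to validity. For scan counts, under an assumed R² of 10-30%, the standard error is about 5-20% too large and the true type I error about 0.015-0.046 against a nominal 0.05. For safety and efficacy, under the assumed rates by difficulty, the intervals are about 1-4% too wide and the power forgone is about one point or less. For performance the power forgone is about 2-3 points at 222 patients and small at 400 or more.

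A reader might infer more than the document supports:

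- **That the trial is underpowered.** It is not on this ground. At the protocol's 20% reduction and at least 200 per arm, unadjusted performance power is about 99% on the plan's own Noether basis.
- **That greater benefit in difficult procedures will be judged by separate tests within subgroups.** The article says only that a subgroup analysis by difficulty will be done. An interaction test is neither stated nor excluded.
- **That leaving t test or Mann-Whitney open is itself an error.** The rule for choosing is mainly analysis-plan detail, and Noether's method is consistent with one of the two named tests.

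**What to change.** Before the database is frozen, state in the analysis plan:

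- **Performance.** One named primary analysis that accounts for centre and difficulty: either a regression of scan counts with both as main effects, or a van Elteren test with small cells pooled. Since the article expects more benefit in difficult procedures, note that van Elteren weights work best when effects are similar across strata.
- **Safety and efficacy.** A risk difference stratified by difficulty (Mantel-Haenszel or stratified Miettinen-Nurminen), with its 90% interval compared with the existing margins. Pool centres, because events are sparse.

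The crude comparisons can stay as sensitivity analyses. The cost is wording and programming: centre and difficulty are both fixed before allocation, and difficulty is entered in the eCRF at that point. The sample size need not change. The small downside is sparse centre-by-difficulty cells, which main effects or pooling handle.

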## Discussion

Navigation assistance systems have demonstrated their value in the fields of orthopaedics, urology and neurosurgery. A previous clinical trial demonstrated that use of the IMACTIS-CT® navigation system during CT-guided interventional procedures improved needle placement accuracy significantly and reduced the number of control CT scans acquired. The aim of the present trial is to address the lack (to the best of our knowledge) of published high-level evidence studies involving evaluation of navigation-assisted, CT-guided interventional procedures. The trial is designed to evaluate the clinical benefit, in terms of safety, efficacy and performance, of navigation-assisted, CT-guided procedures. It is expected that the more accurate needle placement achieved using the navigation system will decrease the procedure duration and decrease the radiation exposure delivered. This trial is important because it addresses the problems associated with conventional CT guidance—inaccurate needle placement, radiation exposure—and is particularly relevant because the number of interventional radiological procedures carried out in routine clinical practice is increasing.

The trial does present certain limitations, however. Firstly, the operators are not stratified according to experience, reducing the comparability of the results in the two groups. However, because the patients are randomly assigned to the experimental or comparator arm, and considering the small number (two to five) of investigators participating in the study per centre, it is expected that the distribution of experienced operators is comparable in both groups. Furthermore, training is provided for the participating radiologists and is obligatory before authorisation is granted to carry out a navigated procedure on a patient enrolled in the trial. Another limitation is that the assignment to the experimental or comparator arm is open label for the radiologist. The assignment cannot be made double-blind, owing to the nature of the procedure. However, the criteria of the primary outcome will be evaluated by a blinded expert committee after the CT scans have been post-processed, such that it cannot be determined whether the scans were acquired in the experimental or comparator arm. A third limitation concerns the absence of respiratory motion tracking integrated into the navigation system; a breath-hold approach is therefore required for certain procedures (e.g., lung procedures). An interesting future perspective is therefore the development and inclusion of respiratory motion management into the system, which is expected to improve the system’s accuracy. Finally, because the navigation system was designed to assist CT-guided interventional procedures, the system has no multi-modal capability.

## Trial status

Patient enrolment started in December 2013 and was expected to be completed before the end of June 2017.

## Abbreviations

AE: Adverse event
CE: Conformité Européenne (European Conformity)
CIC-IT: Clinical Investigation Centre for Innovative Technology
CRA: Clinical research assistant
CT: Computed tomography
CT group: Active comparator arm in which procedures are carried out guided by conventional computed tomography
eCRF: Electronic case report form
ITT: Intention to treat
MRI: Magnetic resonance imaging
NAV group: Experimental arm of the trial in which procedures are carried out using navigation assistance
PP: Per protocol
SIR: Society of Interventional Radiology
SPIRIT: Standard Protocol Items: Recommendations for Interventional Trials
TIMC-IMAG: Techniques de l’Ingénierie Médicale et de la Complexité – Informatique, Mathématiques et Applications, Grenoble (Medical Engineering and Complexity Techniques – Computer Science, Mathematics and Applications, Grenoble)
TSC: Trial steering committee
US: Ultrasound
